### Technological solution

2.3

The telerehabilitation intervention will be delivered using the Khymeia Virtual Reality Rehabilitation System (VRRS; Khymeia Group, Noventa Padovana, Italy), a CE-marked Class I medical device designed to support technology-assisted rehabilitation in clinical and home settings (28–34). In TeleRiab4FRA, VRRS will be configured as a hub-and-spoke architecture in which the clinical TeleCockpit represents the professional hub and each VRRS Home Kit represents a patient-side node. The system will support synchronous, remotely supervised sensorimotor and cognitive rehabilitation, physiological monitoring, treatment assignment, adherence tracking, and review of performance data (Table 3).

**Table 3 T3:** Components and functions of the telerehabilitation system used in the TeleRiab4FRA study. BP, blood pressure; ECG, electrocardiographic; HR, heart rate; K-RING, Khymeia Ring sensor; K-SENSOR, Khymeia inertial sensor; K-SPIRO, Khymeia spirometer; SpO₂, peripheral oxygen saturation; VRRS, Virtual Reality Rehabilitation System.

Component	Main function	Use in the TeleRiab4FRA study
VRRS platform	Digital rehabilitation environment for remote delivery of personalized exercises	Delivery of synchronous sensorimotor and cognitive telerehabilitation sessions
TeleCockpit station	Professional workstation for remote session management and clinical supervision	Used by the rehabilitation team to supervise patients, manage sessions, and monitor rehabilitation activities
VRRS Home Kit	Home-based telerehabilitation kit	Enables patients to perform supervised rehabilitation sessions at home
Tablet device	Patient-side interface for audio-video communication and exercise delivery	Allows real-time interaction between patient and rehabilitation professional
K-SENSOR	Inertial sensors for movement tracking	Monitors movement execution, exercise performance, and adherence during motor training
K-Sensor bands	Supports correct positioning of inertial sensors	Facilitates accurate and reproducible sensor placement on the patient's limbs
K-RING	Wearable sensor for heart rate and peripheral oxygen saturation monitoring	Supports physiological monitoring during home-based sessions
K-SPIRO	Spirometer for guided respiratory exercises	Used for breathing exercises and respiratory components of the rehabilitation program
Health Monitor	Device for measuring and storing blood pressure and single-lead electrocardiographic data	Supports cardiovascular monitoring and safety assessment during the telerehabilitation pathway
Kloud service module	Web-based service for data sharing, treatment assignment, and remote monitoring	Allows centralized management of rehabilitation protocols, session data, adherence, and patient progress
Remote technical support	Assistance for device use and troubleshooting	Supports patients and caregivers in case of technical or connectivity issues

Before starting the home-based program, participants allocated to the telerehabilitation group will complete an initial in-person familiarization phase. During this phase, patients and caregivers will be trained in the use of the platform, wearable devices, respiratory tools, and safety procedures. This preliminary training will be used to verify the patient's ability to interact with the system, ensure correct device placement, and identify the need for caregiver support during the home-based intervention.

The technological infrastructure includes a professional TeleCockpit station used by the rehabilitation team to schedule and manage sessions, assign individualized exercises, establish encrypted audio-video communication, remotely supervise patients, and visualize incoming physiological and performance data. The patient-side configuration includes a VRRS Home Kit with a tablet-based interface and connected sensors. During a synchronous session, the prescribed exercise is transmitted to the patient interface; movement and physiological signals are acquired by the connected devices and made available to the supervising professional through the platform. Session metadata, completion status, exercise parameters, and available sensor outputs are stored within the system and can subsequently be reviewed through the Kloud service module. The architecture therefore supports a bidirectional data flow: treatment instructions and parameter updates move from the clinician to the home unit, while adherence, performance, symptoms, and physiological measurements move from the home unit to the clinical workstation.

The VRRS Home Kit includes inertial sensors for movement tracking, wearable sensors for heart rate and peripheral oxygen saturation, a spirometer for guided respiratory exercises, and a health monitor for blood pressure and single-lead electrocardiographic data. Movement sensors provide information on exercise execution and task completion, whereas physiological devices support safety surveillance and evaluation of exercise response. Data are reviewed in real time during synchronous sessions when technically available; session records and stored measurements can also be reviewed after the session. The platform does not autonomously diagnose clinical deterioration: all alerts, abnormal values, or performance concerns are interpreted by qualified healthcare professionals according to the study safety procedures.

Personalization is clinician-driven and follows prespecified clinical rules. At baseline, the rehabilitation team selects the motor and cognitive modules, session frequency, task complexity, exercise intensity, and progression targets according to CPET results, NYHA class, frailty profile, SPPB performance, cognitive status, comorbidities, and exercise tolerance. During the intervention, the clinician may progress, maintain, simplify, or interrupt an activity on the basis of observed execution, Borg-rated exertion, symptoms, vital-sign response, completion rate, and changes in functional status. Modifications are documented in the treatment record. Thus, the platform functions as a delivery, monitoring, and decision-support environment, while responsibility for personalization remains with the rehabilitation professional.

To improve usability in older frail and pre-frail patients, the technological pathway includes structured patient and caregiver education, simplified instructions for device use, and remote technical support when required. In case of technical issues, poor connectivity, difficulty in using the devices, abnormal clinical parameters, or symptoms suggestive of clinical instability, the session can be interrupted and the patient can be contacted for further assessment. If needed, the patient may be referred for in-person clinical evaluation to ensure safety and continuity of care.

All data collected through the telerehabilitation platform will be managed according to applicable data protection regulations and stored in a secure digital environment. Access will be role-based and restricted to authorized members of the clinical and research teams. Patient identifiers used for clinical management will be separated from the coded research dataset used for analysis. The platform records session dates, assigned activities, completion, available sensor measurements, and technical or clinical interruptions, thereby supporting traceability, adherence assessment, and audit of intervention fidelity.

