### Groups and interventions

2.2

After completion of the baseline assessment, participants will be randomly assigned to one of two study arms: the telerehabilitation group or the control group. Both groups will receive an 8-week individualized rehabilitation program including motor and cognitive training. The rehabilitation content will be tailored according to each participant's frailty profile, while the main difference between groups will be the mode of delivery, supervision, and monitoring.

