#### Telerehabilitation group

2.2.1

Participants allocated to the telerehabilitation group will receive an 8-week synchronous high-technology telerehabilitation program delivered through a CE-marked digital platform. The intervention will combine sensorimotor and cognitive training and will be remotely supervised by qualified healthcare professionals. Before starting the home-based telerehabilitation program, patients and caregivers will receive in-person training on the use of the platform and devices, together with technical instructions and safety procedures.

The telerehabilitation system will allow real-time audio-video interaction between the patient and the rehabilitation team, remote supervision of exercise execution, and monitoring of relevant clinical parameters, including electrocardiographic tracing, heart rate, peripheral oxygen saturation, and blood pressure. Remote monitoring will be used to support safety during the sessions, guide exercise progression, and identify any clinical or technical issue requiring intervention. In case of abnormal clinical parameters, symptoms, or difficulties in performing the exercises, the session may be interrupted and the patient may be referred for additional clinical evaluation.

The motor training program will last approximately 60 min per session, including warm-up, active training, and cool-down. Exercise intensity will be individualized according to baseline CPET findings, with a target progressing toward approximately 70% of baseline VO₂peak; when CPET-based prescription is not feasible, 75%–80% of the maximum heart rate recorded during ergometric testing will be used. The prescription will be progressively adapted to exercise tolerance, clinical status, and frailty level. The cognitive training component will last approximately 30 min per session and will include exercises targeting memory, visuospatial abilities, executive functions, and psychomotor speed.

Training load, task complexity, and exercise duration may be increased when the participant completes the prescribed activities with correct execution, acceptable perceived exertion, stable symptoms, and physiological values within the study safety thresholds. The load will be maintained, reduced, or the session interrupted in the presence of excessive Borg-rated exertion, relevant symptoms, abnormal vital signs, unsafe movement execution, or incomplete recovery. All adaptations and their reasons will be recorded by the treating professional.

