#### Intervention standardization and safety

2.2.3

In both groups, the rehabilitation program will be individualized according to baseline clinical status, frailty level, functional capacity, and exercise tolerance. A common intervention manual will define the motor and cognitive content, target session duration, frailty-based frequency, progression criteria, warning signs, and permitted adaptations. This approach is intended to maintain comparability of rehabilitation dose and content while preserving the specific features of each delivery model. Fidelity in the telerehabilitation group will be assessed through platform logs, session attendance, sensor-derived performance data, and therapist records; fidelity in the control group will be assessed through caregiver competency checks, weekly structured contacts, and review of daily diaries. Participants will continue optimized medical therapy and usual care for CHF throughout the study period.

Safety procedures will be applied in both groups, and both patients and caregivers will be instructed to stop exercise in case of chest pain, marked dyspnea, dizziness, excessive fatigue, palpitations, abnormal vital parameters, or any other concerning symptom. Any adverse event, protocol deviation, or clinically relevant issue occurring during the intervention period will be recorded in the study Case Report Form (CRF) and managed according to Good Clinical Practice principles and local clinical procedures (Table 2).

**Table 2 T2:** Comparison between the telerehabilitation and control interventions.

Feature	Telerehabilitation group	Control group
Intervention duration	8 weeks	8 weeks
Setting	Home-based, synchronous telerehabilitation	Home-based rehabilitation
Delivery mode	Real-time supervision through a digital telerehabilitation platform	Exercises initially explained in person and subsequently performed at home
Supervision	Remote supervision by qualified healthcare professionals	Supervision by caregiver or family member
Rehabilitation components	Motor training and cognitive training	Motor training and cognitive training
Motor training duration	Approximately 60 min per session, including warm-up, active training, and cool-down	Approximately 60 min per session, including warm-up, active training, and cool-down
Cognitive training duration	Approximately 30 min per session	Approximately 30 min per session

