The main scientific contribution of this protocol is the integration of frailty assessment into a multidimensional cardiac telerehabilitation pathway. Rather than evaluating HF rehabilitation only through conventional cardiorespiratory outcomes, TeleRiab4FRA combines VO₂peak with multidimensional measures such as the IFI, SPPB, cognitive screening tools, quality of life, caregiver-related scales, adherence, usability, and safety. This approach may help clarify whether improvements in aerobic capacity are accompanied by changes in broader domains that are particularly relevant in older frail patients.

A further relevant contribution is the comparison between two structured home-based rehabilitation models. The control group receives caregiver-supervised home-based rehabilitation, while the intervention group receives comparable intended rehabilitation content and treatment frequency through a synchronous digital platform with remote professional supervision and clinical monitoring.

This active-comparator design differs from studies in which telerehabilitation has been compared with usual care, no structured rehabilitation, or remote patient management alone. For example, Lundgren et al. compared synchronous home-based exercise with standard care (51), whereas Tele-ADHF compared telerehabilitation plus remote patient management with remote patient management alone (17). The TeleRiab4FRA design is therefore intended to isolate more specifically the added value of synchronous professional supervision, sensor-based physiological and movement monitoring, immediate feedback, and platform-supported personalization beyond the effects of home exercise itself.

The intervention also reflects a multidimensional rehabilitation model. The combination of motor, cognitive, and respiratory training is particularly relevant in frail patients with CHF, in whom physical vulnerability, cognitive difficulties, reduced self-management capacity, and dependence on caregivers may coexist.

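### Respiratory exercise is described only for the telerehabilitation arm, which conflicts with a control programme presented as matched for content

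*Protocol article*

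**What the plan says.** **Passages that give the telerehabilitation arm a respiratory component**
- Section 2.3, Table 3, on the spirometer's use in the study: "Used for breathing exercises and respiratory components of the rehabilitation program".
- Section 2.3, text: the home kit contains "a spirometer for guided respiratory exercises", and before home treatment the telerehabilitation participants and their caregivers are "trained in the use of the platform, wearable devices, respiratory tools, and safety procedures".
- Section 4 (Discussion), on the intervention: "The combination of motor, cognitive, and respiratory training is particularly relevant in frail patients with CHF".

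**Passages that leave it out**
- Table 2 (Section 2.2.3) gives the rehabilitation components as "Motor training and cognitive training", with the same entry in both columns.
- Section 2.2.2 describes the control programme as motor and cognitive exercise, comparable to the other arm in content and duration.
- Section 2.2.3 says that the common manual sets motor and cognitive content. It does not mention respiratory content.

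**Passages that depend on the match**
- Section 2.2 states that "the main difference between groups will be the mode of delivery, supervision, and monitoring".
- Sections 1, 2.1 and 6 describe the control programme as matched for content.
- Section 4 says that the design is "intended to isolate more specifically the added value of synchronous professional supervision". The sentence goes on to add sensor-based monitoring, immediate feedback and platform-supported personalization, all over and above home exercise itself.

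**The concern.** The active comparator is there to hold rehabilitation content constant, so that a difference in VO₂peak can be read as the added value of the delivery model. Respiratory exercise is content. It is not supervision, monitoring, feedback or personalization. If one arm has it and the other does not, the comparison also contains a treatment component that the stated research question excludes.

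The randomized comparison of the two arms stays valid as a comparison of what each arm received. What is at stake is attribution. A positive result could be reported as the benefit of synchronous professional supervision when part of it came from a different programme. A null result would have the same difficulty in reverse.

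**Working it through.** The plan gives no figure for this component, so the main check sets the passages against each other.

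**Step 1. Which readings fit the text?**
- *Respiratory exercise in the telerehabilitation arm only.* The components row of Table 2 is then incomplete in one column, and the statements that the control is matched for content are wrong.
- *Respiratory exercise in both arms.* Table 2 is then incomplete in both columns, as are Section 2.2.2 and the description of the manual. The spirometer belongs to the telerehabilitation kit, and the technology row of Table 2 gives controls only a diary and caregiver support, so how controls would do the exercises is not stated.
- *Not a component in its own right in either arm.* The Discussion sentence and the Table 3 entry then overstate it.

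Under every reading at least one passage has to change.

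**Step 2. Session time.** Both arms have about 60 minutes of motor and 30 minutes of cognitive training per session. No time is assigned to breathing exercise. It could sit inside the motor hour or be added to it, and the text does not say which.

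**Step 3. What the analysis can recover.** Write the between-arm difference at 8 weeks as

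Δ = D + R,

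where D is the effect of supervision, monitoring, feedback and platform-supported personalization, and R is the effect of respiratory exercise. If only one arm receives it, the indicator for R equals the indicator for treatment group. ANCOVA with baseline VO₂peak, the mixed model and the per-protocol analysis (at least 80% of sessions completed) then each estimate the sum and cannot estimate D alone. Relating the outcome to breathing sessions completed within the telerehabilitation arm would be a non-randomized comparison.

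**Step 4. Sample size (Section 2.6.3).** The inputs are a difference of 2.5 and an SD of 3.5 mL/kg/min, two-sided α = 0.05 and 80% power. Then d = 2.5/3.5 = 0.714. The normal approximation gives 31 per group. The exact t-test gives 32 at d = 0.714 and 33 at d = 0.71, so the stated 33 is reproduced. Nothing in this point changes it.

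**Step 5. Illustration under assumed values of R.** Suppose D = 0 and R = b, with 33 per group and SD 3.5. The noncentrality of the t-test is (b/3.5) × √(33/2) = (b/3.5) × 4.062 on 64 degrees of freedom.
- b = 0.5: 0.58, significant in 8.8% of trials
- b = 1.0: 1.16, significant in 20.8%
- b = 1.5: 1.74, significant in 40.3%
- b = 2.0: 2.32, significant in 62.8%

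The nominal rate is 5%. None of these values of b comes from the documents. They show only how an unmatched component would enter the result.

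**The case against.** The best defence is that this is loose labelling in a condensed article. Table 3 is an inventory of telerehabilitation equipment, so controls would not appear in it. Table 2 does not list respiratory work as a separate component even for telerehabilitation. Breathing exercise could be part of the motor session in both arms, and no passage excludes it for controls. Section 2.2 speaks of the main difference, not the only one, and Section 2.2.3 aims at comparable dose and content while keeping the specific features of each model. The isolation claim is expressed as an intention and covers more than supervision.

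Much of this stands. It is not shown that controls go without respiratory exercise, and the isolation claim is weakened rather than refuted. But Table 2 exists to compare the arms and makes a positive statement about components, which the Discussion contradicts by naming a third. That is a conflict between statements, not a detail left to a fuller document. The breadth of the isolation claim does not help either, because respiratory exercise is not among the features it lists.

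A reader might also infer a mismatch in exercise intensity, since a numerical prescription, "with a target progressing toward approximately 70% of baseline VO₂peak", appears only under the telerehabilitation heading. The documents do not support calling this a contradiction. No passage gives controls a different target or none. Table 2 tailors both arms to baseline functional capacity and exercise tolerance in identical words, and one manual sets progression criteria for both. Whether the prescription applies to controls is unclear, and that calls only for clarification.

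**Conclusion.** The point holds for respiratory exercise. The article gives the telerehabilitation arm a component that its own comparison table, control description and manual scope omit, while describing the control as matched for content. As written, the match is unsupported, and a difference in VO₂peak could not be credited specifically to the delivery model.

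The size cannot be computed from the documents. A reader might put a share on it: an assumed 0.5 to 1.0 mL/kg/min would be 0.5/2.5 = 20% to 1.0/2.5 = 40% of the planned difference. Nothing in the documents supports that range, or shows that respiratory exercise moves VO₂peak in this population, so the verdict does not rest on it. It rests on the conflict between the passages and on the fact that a component given to one arm only cannot be separated from allocation. The sample size and the test of one arm against the other are unaffected; what changes is what the trial may conclude.

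**What to change.** 1. Reconcile Sections 2.2, 2.2.2, 2.2.3 (with Table 2), 2.3 (with Table 3), 4 and 6, and carry the result into the matching statements in Sections 1 and 2.1. Table 2 should state for each arm whether respiratory exercise is part of the programme.
2. As a clarification only, state whether the intensity prescription in Section 2.2.1 applies to both arms.
3. If respiratory exercise remains in one arm only, replace the content-matching and isolation wording. Say instead that the trial estimates the effect of the whole telerehabilitation package, including respiratory training, against the caregiver-supervised programme.
4. Summarise delivered respiratory exercise by arm. The planned records should allow this: platform and therapist records in one arm, daily diaries in the other.

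Which content each arm receives is the sponsor's clinical decision, and none is proposed here. The cost is some wording, one or two rows in Table 2 and, if the difference stays, a less specific claim. No extra participants, visits or analyses of the primary endpoint are needed. It is best done early, because content already delivered cannot be equalised afterwards.
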